#### Study 2: Reward processing

The second fMRI study will investigate how treatment expectation modulates activity in brain regions involved in reward processing in patients with MDD. Following the same expectation induction and treatment procedure as summarized above and detailed in “Experimental design,” the patients will perform a monetary incentive delay task (MID; [31]) during fMRI (see “fMRI paradigms” below and Fig. 1). Here the patients will be cued to anticipate and respond to a rapidly presented target in order to gain or avoid losing varying amounts of money. The same measures of treatment expectation, depressive symptoms and treatment related side-effects as described in Study 1 will be employed.

#### Hypotheses

Positive treatment expectation (high/low) in MDD will result in enhanced VMPFC activation during reward processing.Baseline activation in regions of the mesolimbic system during reward processing (in particular hippocampus, NAc) will be predictive of 4-h and 1-week treatment effects.High vs low treatment expectations in MDD will differentially affect VMPFC activation during reward processing.More specifically, we expect that the interaction of treatment expectation and treatment indicates most pronounced effects in the high expectation + verum group and lowest in the low expectation + placebo group (high + verum > low + verum ≥ high + placebo > low + placebo).Baseline VMPFC and rACC functional (rsfMRI) and structural (DTI) connectivity with hippocampus predicts placebo treatment response after 4 h [24].

#### Experimental design

##### Factor 1 Medication (esketamine vs placebo)

The study drug will be provided as a solution for infusion/injection. Each device delivers either esketamine hydrochloride (0.25 mg/kg of esketamine) or placebo (sodium chloride 0.9%). Placebo and verum treatment will be provided via identical devices which will be prepared and delivered by a dedicated clinical trial pharmacy not involved in any of the other procedures in the trial. None of the patients, research staff or clinical staff will be informed about the patient assignment throughout the trial. Blinding will also be maintained throughout the statistical analysis. This has proven the most efficient dose with tolerable side effects in a previous trial [24]. Details on the procedure used in this trial can be found under the following link: https://www.sciencedirect.com/science/article/abs/pii/S0165032719319780?via%3Dihub.

Patients will be monitored for 4 h in the Department of Psychiatry, Philipps-Universität Marburg following administration, including continuous vital signs monitoring (i.e. heart rate, blood pressure, respiration and pulse oximetry).

##### Factor 2 Expectation (high/low)

While all patients will be correctly and non-deceptively informed that they are going to be randomized to placebo or verum, treatment expectation will be varied by providing incorrect probabilities for this randomization. In the high expectation group, participants will be (deceptively) informed that the study medication most likely (90%) contains the active drug, while the low expectation group will be (deceptively) informed that it is very unlikely (10%) that the study medication contains the active drug, but placebo [34]. One hour after expectation induction and receiving the study medication, patients will undergo MRI measurements: T1, DTI, fMRI resting state and two experimental “fMRI paradigms” addressing emotional and reward processing: (1) implicit processing (gender judgement) of positive and negative emotional faces (emotion processing) and (2) reward processing [31]. The paradigms are chosen because they (i) investigate emotional-cognitive-behavioural processes relevant for expectation formation and they reliably activate brain networks implicated in (ii) MDD, (iii) its treatment effects and (iv) placebo response in previous studies. Psychometric assessments at baseline will include BDI, MADRS, YMRS, expectation scale, dissociative experience scale and GASE. After pharmacological challenge assessments will include BDI, MADRS, YMRS, dissociative experience scale, GASE at 40 min, 4 h, 24 h, 3 days (+ expectation scale) and 7 days (+ expectation scale) after treatment (cf. “Data collection and management” section; adapted versions for symptom assessment at present will be used for assessments from 40 min to 3 days post-dose.) Treatment outcome in response to expectation and drug treatment will be assessed at the behavioural, subjective and neural level. After the end of the study (day 7 after final study assessments), the participants will be informed about the deception.

#### fMRI paradigms

##### Study 1: Emotion processing task

This modified version of the task used by Surguladze et al. [9] involves the presentation of grayscale faces with happy or fearful expressions in 16.8-s blocks of 10 pictures each, with each picture presented for 1.5 s, followed by 200 ms blank screen. There will be sixteen 16.8-s blocks with facial expressions (10 fear, 10 happy), and each block will be followed by a 16.8-s baseline block during which a fixation cross will be presented (ACBC block design). The face stimuli (60 individuals, each showing the two different emotions) were selected from the Karolinska Directed Emotional Faces (KDEF) dataset (http://www.emotionlab.se/resources/kdef). On presentation of each facial expression, patients will be required to indicate whether the face is a male/female by pressing the left (female)/right (male) button on a button box, simply to ensure they are attending to the stimuli. During baseline, the patients will be instructed to press the button for each cross presented for 1.5 s, followed by 200 ms blank screen.

##### Study 2: Reward processing

Patients will perform a “Monetary Incentive Delay” (MID) Task [31]. Each of two MID task runs consist of 90 6-s trials, yielding a total of 180 trials. During each trial, patients will see one of nine cue shapes (cue; 250 ms), fixate on a crosshair as they wait a variable interval (anticipation; 2000–2500 ms), and then attempt to respond with a button press during the presentation of a white target of variable duration (target; 80–360 ms). Feedback (outcome; 1650 ms) will follow the disappearance of the target, which will notify subjects how much money they had gained or lost that trial as well as their cumulative total up to that point. On incentive trials, subjects can either gain or avoid losing money by pressing the button during target presentation. Task difficulty will be based on reaction times collected during a practice session prior to scanning and set such that participants will succeed on approximately 66% of their target responses. Cues signal potential gains (*n* = 72, denoted by circles), potential losses (*n* = 72; denoted by squares) or no response requirement (*n* = 36; denoted by triangles). Gain cues signal the possibility of winning 0.00 € (*n* = 18; no lines), 0.20 € (*n* = 18; one horizontal line), 1.00 € (*n* = 18; two horizontal lines), or 5.00 € (*n* = 18; three horizontal lines). Similarly, loss cues signal the possibility of losing 0.00 € (*n* = 18; no lines), 0.20 € (*n* = 18; one horizontal line), 1.00 € (*n* = 18; two horizontal lines), or 5.00 € (*n* = 18; three horizontal lines). “No response” trials (*n* = 36; a triangle) indicate that the subject should not respond during that trial, and instead should wait until the cue signaling the next trial appears. Trial types will be pseudo-randomly ordered within each run and runs will be counterbalanced across subjects. Patients will be trained for at least 10 min and tested for explicit cue comprehension. After the trial, the patients will receive the money they have won during the task on top of their participant’s reimbursement.

#### Psychometric measures

All participants will undergo a standardized assessment of sociodemographic and psychological trait and state characteristics using paralleled instruments. These include acute and chronic stress levels, negative affect, anxiety and depression. Further, an individual’s treatment expectation and prior treatment experiences in general and with antidepressant treatments in particular will be assessed. A description of these measures is described in the “Data collection and management” section. At the study-specific level, assessment of depression symptoms (BDI, MADRS; adapted versions referring to symptoms at present will be used for assessments from 40 min to 3 days post-dose) will be taken repeatedly as part of the treatment efficacy assessment (on day 1 (predose and 40 min post dose), 4 h, 24 h, 3 days, 7 days, Fig. 1). Study-specific treatment safety assessments will include monitoring of adverse events (ECG, blood pressure, blood oxygen level) and treatment related side effects using the Clinician Administered Dissociative States Scale (CADSS; [35]) and Young Mania Rating Scale (YMRS; [36]) on day 1 (predose, 40 min, 2 h and 4 h post dose; adapted versions referring to symptoms at present will be used for assessments from 40 min to 3 days post-dose).

### Criteria for discontinuing or modifying allocated interventions {11b}

The intervention will be discontinued in response to harms, participant withdrawal of consent, or worsening condition.

### Strategies to improve adherence to interventions {11c}

No strategies to improve adherence to interventions have been put in place as the intervention consists of a single dose only.

### Relevant concomitant care permitted or prohibited during the trial {11d}

Best medical care according to guidelines will be given to all patients. The proposed study will not interfere with the patients’ treatments. Patients are treated according to S3 guidelines for treatment of depression. This includes both medication and state-of the-art psychological therapies.

### Provisions for post-trial care {30}

Following administration of the study medication, patients will be monitored for 4 h in the Department of Psychiatry, Philipps-Universität Marburg including continuous vital signs monitoring (i.e. heart rate, ECG, blood pressure, respiration and pulse oximetry). No provisions for post-trial care planned. For all patients in this trial, an insurance covering possible damage to the patients and an accident insurance is contracted at the Gerling Industrie Versicherung AG, Insurance number: 57 010312 03019/03262. This patient insurance covers any damage to health arising from participation in the study up to a maximum sum. In order not to violate the insurance cover, the patient must immediately notify the insurance company or the investigator in case of any damage to health arising from participation in the clinical study. A copy of the complete insurance terms and conditions will be made available to the patient. In addition the accident insurance covering accidents on the way to and from the study centre.

### Outcomes {12}

Primary outcome measures include:Brain activation in networks implicated in (i) reward and (ii) emotion processing, (iii) placebo and (iv) antidepressant treatment response in MDD and (v) the pathophysiology of MDD (in particular VMPFC, rACC, amygdala, hippocampus).

Secondary outcomes include:Behavioural reaction times and hit rates in the Monetary Incentive Delay task (see Study 2: Reward processing)Expectation-related changes in depressive symptoms (self-rating BDI, expert rating MADRS) in response to placebo and esketamine.

Primary outcomes will be assessed 1 h post treatment, secondary outcomes at 1h, 2h, 4h, 24 h, 3days and 7days post treatment.

### Participant timeline {13}

The SPIRIT participant timeline for the study can be seen in Table 1.

### Sample size {14}

Performing power calculations for voxelwise imaging data is problematic because of the large number of measures examined (typically > 100,000 voxels). In addition, even with appropriate correction for multiple comparisons, effect sizes from voxel-wise imaging data are inflated leading to erroneous estimates of required sample sizes. Thus investigators in the field often use previous studies as a guide to the number of subjects needed to recruit. To date, only very few previous studies [30, 32, 33] with sample sizes ranging between *N* = 10 and *N* = 37 have used fMRI to investigate the effects of i.v. ketamine on the functioning of neural networks related to reward processing in 10 patients with treatment-resistant MDD (cf. our primary outcomes; [30]). This study found that the improvement in mood was accompanied by an increased recruitment of the orbitofrontal cortex, ventral striatum, medial substantial nigra and ventral tegmental area, structures that are part of the reward circuitry. However, these studies either did only include patients with treatment-resistant MDD [30, 33], no placebo condition [30] or only included patients in remission [32]. A recent cross-sectional fMRI study on the effects of ketamine vs placebo on the processing of happy vs angry facial expressions in patients with MDD [27] reported robust effects in brain regions relevant for emotion processing (particularly the amygdala) with 33 patients which is comparable to the numbers we are planning to recruit in our study (4 groups, each comprising 36 patients each + 20% dropout = 4 × 44 patients = 176 patients). This sample size calculation is substantiated by a power analysis of behavioural effects (cf. our secondary outcomes): To be on the conservative side, we have powered the present study to detect small-to-medium effect sizes (*d* = 0.40) of the expectation manipulation including interactions with behavioural reaction times and hit rates in the Monetary Incentive Delay task (see Study 2: Reward processing), assuming an alpha of 5% and a power of 90% which results in a required sample size of *N* = 36 per group (4 groups, each comprising 36 patients each + 20% dropout = 4 × 44 patients = 176 patients).

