**Fig. 1 Fig1:**
[figure not shown]
Study design. One hundred seventy-six patients with acute MDD will be recruited (d-3), undergo baseline assessment (d0_1_), female participants of child bearing age will undergo a serum pregnancy test (d-3). At d1, patients will be randomized into 4 groups with the factors treatment (esketamine/placebo) and expectation (high/low). They will take part in two fMRI studies, rsfMRI, DTI and T1 scanning. Clinical outcomes will be assessed after 2 h, 4 h (all d1), 24 h (d2), 3d and 7d post treatment. Urine pregnancy tests will be performed at day 28

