## Assignment of interventions: allocation

### Sequence generation {16a}

Patients will be randomized into one of the four experimental conditions (*n* = 4 × 44) using a balanced randomization procedure using block randomization. The block size will be randomly varied to reduce the likelihood of foreknowledge of treatment assignment among those recruiting participants.

Randomization and allocation sequence will be performed centrally by the central office of the Coordinating Center for Clinical Trials in Marburg (Koordinierungszentrum für klinische Studien (KKS/CCCT). Variations in block sizes will be performed by the KKS unbeknownst to those who enroll participants or assign interventions. The randomization of an eligible patient can take place if all inclusion criteria and none of the exclusion criteria are fulfilled. Therefore the investigator completes the study specific randomization form, which is part of the Investigator Site File (ISF), and sends it to the KKS Marburg via fax. The chance for allocation to the 4 groups is 1:1:1:1. The KKS reports the randomization result in form of a “medication number plus expectation induction” back to the centre. In the following, the pharmacist at centre has to note the centre-specific patient pseudonym on the medication and the emergency envelope which are already labeled with the corresponding package number.

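### The 36 patients per group cannot be reproduced from d = 0.40, alpha 5% and power 90%; a simple between-patient expectation effect has about 66% power

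*Protocol article*

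**What the plan says.** Sample size {14} gives no power calculation for the primary fMRI outcomes. It explains why voxelwise calculations are problematic and relies on the size of an earlier study. It then supports the number with a power analysis of secondary outcomes, reaction times and hit rates in the Monetary Incentive Delay (MID) task. The target is "small-to-medium effect sizes (*d* = 0.40) of the expectation manipulation including interactions with behavioural reaction times and hit rates", "assuming an alpha of 5% and a power of 90% which results in a required sample size of" 36 per group. The total follows as "4 groups, each comprising 36 patients each + 20% dropout = 4 × 44 patients = 176 patients". The choice of effect size is described as conservative.

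Two other places fix the design. The legend of Fig. 1 says "patients will be randomized into 4 groups with the factors treatment (esketamine/placebo) and expectation (high/low", and Sequence generation {16a} says "The chance for allocation to the 4 groups is 1:1:1:1". Expectation is therefore a between-patient factor with two of the four groups at each level.

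The power analysis names no test, sidedness, number of repeated measures, within-patient correlation or covariate.

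**The concern.** The sentence presents 36 as the result of three printed inputs, and the usual calculation from those inputs gives a very different number. It is the only quantitative support for the sample size. The effect it covers, expectation and its interplay with esketamine, is the subject of the trial.

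The risk lies in how a null result would be read. With 90% power, a true effect of 0.40 SD is missed one time in ten. With 66% power it is missed about one time in three (34%).

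**Working it through.** **Inputs.** From Sample size {14}: d = 0.40, alpha 5%, power 90%, 36 evaluable per group (4 x 36 = 144), 20% dropout, 44 per group randomised. From Fig. 1 and Sequence generation {16a}: 2 x 2 between-patient factors, 1:1:1:1. Assumed: SD = 1 on the d scale, two-sided test unless stated, no covariate gain. Power is from the noncentral t or F distribution.

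**Attempt to reproduce 36.**
- Two groups, normal approximation: n = 2(1.960 + 1.282)² / 0.40² = 131.3, so 132 per compared group (108 one-sided). The noncentral t gives 133, which is about 67 per cell.
- 0.40 read as Cohen's f: 68 patients in total for a 1-df effect and 93 for a 3-df effect (96 with equal cells), not 144.
- Paired or one-sample test: 68 patients.

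None of these gives 36 per group.

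**Power with 36 per cell.**
- Expectation main effect, 72 v 72: SE = √(2/72) = 0.1667; noncentrality 0.40/0.1667 = 2.40 on 140 df; power **66.4%** (one-sided 77.1%). With all 176 evaluable (88 v 88) it is 75.1%.
- Detectable at 90%: d = 0.544.
- One pair of cells, 36 v 36: 38.8% (one-sided 51.4%).
- Expectation-by-drug interaction, 0.40 SD as the difference of differences: SE = √(4/36) = 0.333; noncentrality 1.20; power **22.2%**. For 90%, 264 per cell are needed.
- The same interaction read as f = 0.20, which is a difference of differences of 0.80 SD: noncentrality 0.80/0.333 = 2.40; power **66.4%**.

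**Repeated-measures readings at N = 144, f = 0.20 (the equivalent of d = 0.40 for two levels).** The numbers of measures (m) and correlations (r) are assumptions; the article gives none.
- Between-patient effect of expectation, λ = f²·N·m / [1 + (m − 1)r], with m = 3:

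| r | λ | Power |
|---|---|---|
| 0.3 | 17.28/1.6 = 10.80 | 90.4% |
| 0.5 | 17.28/2.0 = 8.64 | 83.1% |
| 0.7 | 17.28/2.4 = 7.20 | 76.0% |

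- Expectation-by-task-condition (within-between) interaction, λ = f²·N·m / (1 − r): two levels, two measures, r = 0 gives λ = 11.52 and 92.1%. Four groups, two measures, r = 0.2 gives λ = 14.40 on 3 df and 89.6%. Here power rises with r.
- A covariate instead of repeated measures would need a correlation of about 0.68 with the outcome to bring the main effect to 90%.

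**Dropout.** 36 x 1.2 = 43.2, taken up to 44. Allowing for a 20% loss means 36/0.8 = 45. Conversely 44 x 0.8 = 35.2, below the required 36. Forty-four per group tolerates 1 − 36/44 = 18.2%, or 8 of 44. With 35.2 per group the main-effect power is 65.4% instead of 66.4%.

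**The case against.** The best defence is that the calculation used a repeated-measures model. The MID task has gain, loss and no-response cues at several amounts, and the interactions that the sentence mentions may be those of expectation with task condition, not with drug. Under a common convention (f = 0.20, two expectation levels, three measures, correlation 0.3) the required total is exactly 144, which is 36 per group. A condensed article may leave the test and the correlation to the full protocol.

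Much of this stands. A reader might infer that the trial flatly fails to deliver 90% power for any effect; the document does not support that, because it names no test and some plausible models reach 90%. A reader might also take 22% as the power for the interaction. That figure holds only if 0.40 SD is the expectation-by-drug difference of differences, and the sentence does not say so.

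The defence does not rescue the sentence as printed. It says that the three inputs result in 36, and they do not. The 90% then depends on inputs that are not given, and for the between-patient effect it falls again as the correlation increases. Whether to report the test is a matter of detail; a stated result that does not follow from its stated inputs is not.

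It is also fair that the primary fMRI outcomes rest on precedent, that Trial design {8} calls the framework exploratory, and that the dropout slip is less than one patient per group.

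**Conclusion.** The point holds in a limited form. The 36 per group is not reproducible from d = 0.40, alpha 5% and 90% power, and 90% is not met for a simple between-patient effect: about 66% two-sided or 77% one-sided with 72 v 72, and 90% only at d of about 0.54. For the expectation-by-drug interaction the range is 22% to 66%, depending on what 0.40 measures. These figures assume one outcome value per patient and no covariate adjustment.

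The sentence should be corrected, but the matter is not critical, because it concerns secondary behavioural outcomes. The dropout error is real and minor.

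**What to change.** Keep 176 patients and change the wording of Sample size {14}.

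- Restate the power for the between-patient effect: with 144 evaluable patients, 66% for an expectation main effect of d = 0.40, or 90% for d = 0.54 (two-sided 5%). Describe the expectation-by-drug interaction as exploratory.
- If a repeated-measures model produced 36, state instead the test, the number of measures, the assumed correlation and the scale on which d is defined. Limit the 90% claim to the effect that the model covers, and still give the between-patient figure.
- Replace the 20% dropout by about 18% (8 of 44), or say that about 35 per group remain evaluable after a 20% loss.

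The cost is a text change. No patients are added and the design is untouched; the stated power becomes less favourable unless the model used is disclosed and supports it.

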### Recruitment {15}

A total of 176 patients with MDD according to DSM-5 criteria will be recruited from in- and outpatient settings from the Department of Psychiatry and Department of Psychology, University of Marburg, the Department of Clinical Psychology, University of Marburg and surrounding psychiatric hospitals. This monocentric study will be conducted as part of the Collaborative Research Center (CRC 289) “Treatment Expectation: The impact of expectation on health outcome” at the Department of Psychiatry and Psychotherapy, Philipps-Universität Marburg. The department has adequate staff and experience in treating patients with MDD and in conducting clinical trials as well as experienced physicians and supportive staff with adequate time, the targeted patient population and technical expertise to complete the protocol. It has a track record in recruiting patients with MDD, first episode psychosis, schizophrenia, anxiety disorders and bipolar disorder to large-scale national and international single- and multi-centre studies involving neuroimaging, deep phenotyping, clinical and cognitive assessments (FOR2107, Panic-Net I, Panic-Net II, PROTECT-AD, BipoLIFE, PSYSCAN, among others).

